### Recruitment

The research team will contact potential participants diagnosed with AN and on the waiting list for admission to the eating disorder unit at UPC Z.Org to schedule an online appointment to receive detailed information about the study and have any questions answered. Subsequently, participants will receive a comprehensive informed consent form outlining the study protocol. Finally, upon hospital admission, the investigator will conduct a final eligibility assessment, and participants (or those under 18, along with parental consent) will provide written consent or assent.

### Randomization and blinding

This study will use computer-generated block randomization with random block sizes of 2 and 4 for participant allocation. There will be no stratification applied during the randomization process. An independent researcher not involved in any aspect of the trial will securely store the allocation sequence. The study will be performed in a triple-blinded manner, such that the researchers, patients, and data analysts remain unaware of treatment allocation until final statistical results are obtained.

### Interventions and concomitant care

We will efficiently deliver SCFAs to the large intestine by utilizing pH-dependent CDCs to mimic the process of dietary fiber fermentation in the colon, as done previously [19]. Participants will consume capsules of a mixture of SCFAs spread at four intervals throughout the day. The SCFA mixture contains acetate, propionate, and butyrate in a ratio of 60:20:20, and the total daily amount of SCFAs is equivalent to the fermentation of 10 g of arabinoxylan oligosaccharides [38]. Microcrystalline cellulose, not absorbed in the gastrointestinal tract, will be included in the same type of CDCs to serve as a placebo. The nursing staff will distribute the capsules to the participants individually, supervise their intake, and monitor adherence by capsule count. Although adverse effects are not expected [19], these will be documented. Participation will be discontinued if the patient exhibits a high medical or psychiatric risk requiring priority or fails to adhere to the consumption of the intervention substances (taking less than 80% of capsules) or to the study procedures.

Participants in both groups will receive treatment as usual, consisting of an inpatient psychotherapeutic program of 12 weeks focusing on nutritional rehabilitation. We will closely monitor the use of other medications throughout the study. However, such usage will not lead to the termination of the trial intervention. After undergoing the intervention and post-intervention visit, if any participant decides to leave the residential program early, we will still aim for a follow-up visit to take place at the hospital.

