## Outcomes

### Primary and secondary outcomes

The primary outcome of this study focuses on the salivary cortisol response to acute laboratory stress. We will examine the change in cortisol levels within and between SCFAs and placebo groups. Crucial secondary outcomes encompass the participants' food choices and nutritional status (BMI). All other measures delineated in the subsequent sections serve as secondary outcome measures. See Table 1 for an overview of scheduled assessments.

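### The rule for taking under 80% of capsules ends study participation, not only capsule intake, so participants discontinued before week 6 supply no post-intervention stress test

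*Protocol article*

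**What the plan says.** All of the relevant rules stand in the protocol article under Interventions and concomitant care.

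- **Who is discontinued.** "Participation will be discontinued if the patient exhibits a high medical or psychiatric risk requiring priority", or if the patient "fails to adhere to the consumption of the intervention substances (taking less than 80% of capsules) or to the study procedures".
- **How adherence is known.** Nursing staff hand out the capsules, "supervise their intake, and monitor adherence by capsule count". Adherence is therefore a post-randomisation measure.
- **Who is followed after leaving.** "After undergoing the intervention and post-intervention visit, if any participant decides to leave the residential program early, we will still aim for a follow-up" visit at the hospital. This is the only commitment to measure people who leave.
- **Separate wording for stopping the product.** On the use of other medication, the section says that "such usage will not lead to the termination of the trial intervention".

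Under Primary and secondary outcomes: "The primary outcome of this study focuses on the salivary cortisol response to acute laboratory stress". The Trier social stress test section places that test at the baseline and post-intervention visits only, and the choice phase of the food choice task follows it directly. Under Statistical methods for primary and secondary outcomes, the group-by-visit and group-by-visit-by-timepoint interactions in linear mixed models are the principal effects.

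**The concern.** The rule makes outcome collection depend on behaviour after randomisation. In anorexia nervosa, refusing capsules or study procedures is plausibly related to weight, eating pathology and stress, which are what the trial measures. If those who stop early are not assessed at week 6, the arms being compared are no longer the arms that were randomised.

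The protocol sets out to examine a causal role for SCFAs, and that claim draws its strength from randomisation. A statistical analysis plan can define analysis sets, but it cannot recover a stress test that was never done. The point therefore concerns a stated rule on data collection, not detail that an article may leave to another document.

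**Working it through.** **1. What is stopped: participation or capsules?** The discontinuation sentence has participation as its subject. Two sentences that are close together use different terms: participation is discontinued in one, and the trial intervention is terminated in the other. The natural reading is that the first means leaving the study.

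**2. Who is then measured?** The follow-up commitment starts only after the intervention and the post-intervention visit. No section provides for assessing someone discontinued before week 6. The stress test and the choice phase of the food choice task have no later occasion, since the follow-up visit comprises weight, questionnaires, food diary and stool sample. Such a participant contributes a baseline but no post-intervention value for cortisol or food choice.

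**3. What may still exist?** Under Other measures and questionnaires, ward staff weigh patients recurrently and questionnaires are also given three weeks into the intervention. BMI and questionnaire outcomes are less exposed.

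**4. The protocol's own power figure.** Inputs from Sample size: N = 80 (40 per arm), f = 0.16, alpha 0.05, power 80%. The correlation between visits is not given; ρ = 0.5 is assumed.

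- λ = f²·N·m/(1 − ρ) = 0.0256 × 80 × 2 / 0.5 = 8.192, with 1 and 78 degrees of freedom.
- Power = 0.807, which reproduces the stated 80%. At ρ = 0.3 it is 0.666, and at ρ = 0.7 it is 0.954.
- In units of the SD of change, the corresponding difference is √(4λ/N) = √(4 × 8.192/80) = 0.64 SD.

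**5. Power under loss (f = 0.16, ρ = 0.5).** The target of 92 less 15% is 92 × 0.85 = 78.2.

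| Participants with week-6 data | Power |
|---|---|
| 92 (all) | 0.859 |
| 78 (15% lost) | 0.797 |
| 73 (a further 5% discontinued) | 0.769 |
| 69 (a further 10%) | 0.745 |
| 64 (a further 15%) | 0.712 |

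The last three rows assume that discontinuations come on top of the 15% allowance. The protocol does not say whether they do. All rows hold f fixed.

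**6. Illustrative bias with no true effect.** The loss rates and correlations are assumptions. If a fraction q with the lowest adherence is removed, and adherence correlates r with the outcome change, the mean of those retained shifts by r·φ(z_q)/(1 − q) SD, where z_q is the q-quantile and φ the density of the standard normal distribution.

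- q = 0.15: φ(−1.036)/0.85 = 0.2332/0.85 = 0.274.
- q = 0.05: φ(−1.645)/0.95 = 0.1031/0.95 = 0.109.
- Difference between arms: 0.274 − 0.109 ≈ 0.166 (unrounded). Multiplied by r = 0.2, 0.3 and 0.5, this gives 0.033, 0.050 and 0.083 SD.
- Type I error, starting from 46 per arm: 39.1 and 43.7 remain, so SE = √(1/39.1 + 1/43.7) = 0.220. The two-sided error is 0.053, 0.056 and 0.066 in place of 0.050.
- 20% against 5%: 0.05 to 0.12 SD, type I error 0.055 to 0.084.
- 10% in both arms with the same r: no bias, type I error 0.050.

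Against the 0.64 SD from step 4, a bias of 0.033 to 0.083 SD is 5% to 13%.

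**The case against.** The other side has several fair points.

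- **Loss of outcomes is read from the text, not stated in it.** The sentence sits in a section on the intervention and does not say when the 80% is judged. If the count is taken only over the full six weeks, the week-6 visit falls due at about the same time. This stands as a reason to clarify. It does not remove the literal meaning, which the separate term for terminating the intervention supports.
- **The design limits differences between arms.** Placebo is given in the same type of capsule, intake is supervised, patients and researchers are blinded, and adverse effects are not expected. This stands, and removals may be few and balanced.
- **The aim is partly mechanistic.** An effect among those who took the capsules is a relevant question. It can be answered by a supplementary analysis without giving up the randomised comparison.
- **Some non-adherers will decline a full-day visit with catheter and stress test.** This also stands; the gain for cortisol may be partial.

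A reader might go further than the documents allow in three ways:

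- One might infer that the trial becomes a per-protocol analysis. No such set is named, and the mixed model can keep the baseline data of discontinued participants.
- One might infer that every outcome of these participants is lost. Ward weights and week-3 questionnaires may exist.
- One might infer that the SCFA effect is overstated by a definite amount, such as 1/0.85 = 1.18 times or 0.15 × 1 SD − 0.05 × 1 SD = 0.10 SD. The first assumes no benefit in anyone below 80%, and the second a full 1 SD deficit in those removed. The documents support neither assumption and fix no direction.

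**Conclusion.** The point holds in a limited form. As written, the protocol ends participation on a post-randomisation criterion and makes no provision to assess those discontinued before week 6. The group-by-visit effect on cortisol and food choice would then be estimated essentially from adherers.

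This creates a risk of bias, not a demonstrated bias. Bias arises only if discontinuation differs between arms in rate or in its link to outcome. At an assumed 15% against 5%, with correlation 0.2 to 0.5, it is about 0.03 to 0.08 SD; with equal loss and the same link it is nil. The direction is unknown, and the protocol gives no expected rates.

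The change is worth making because the rule discards the data that would show whether bias occurred, and later analysis cannot restore them. The discontinuation for medical or psychiatric risk is a clinical matter and is not judged here.

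**What to change.** Leave the rules on stopping capsules and on medical or psychiatric risk as they are, and amend the section in three respects:

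1. State that stopping capsules, or falling below 80%, is separate from leaving the study. Invite every randomised participant who still consents to the scheduled week-6 and week-12 assessments: at minimum weight and questionnaires, with the stress test where the investigator judges it acceptable.
2. Extend the follow-up sentence to participants who leave before week 6.
3. Analyse all these participants in their randomised arm, and report the set taking at least 80% of capsules as a supplementary analysis.

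The cost is a short amendment and a small effort to contact leavers. The visits are already scheduled, the inpatient programme lasts 12 weeks, and weights are taken on the ward. No larger sample is needed. Keeping non-adherers may dilute the effect estimate, by an amount for which the protocol gives no figure. The amendment has to come while participants can still be followed.

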### Study visits

#### Baseline and post-intervention visit

Participants will be asked to collect a stool sample during the first three days of hospitalization—before the start of the intervention—and the three days preceding their second study visit. We will instruct them to refrain from vigorous physical activity, alcohol, and caffeine one day before the visits to prevent interference with the scheduled tasks. To standardize fiber intake, the participants will receive a low-fiber standardized dinner the night before each visit and a low-fiber breakfast and lunch on the day of the visits. Low-fiber snacks on both visits will replace the snacks provided on the ward at 10:30 and 15:00. Participants will keep an electronic food diary (Nutritics software) for three days during their initial hospitalization and three days before their second study visit to monitor their macronutrient and energy intake. To avoid encouraging disordered eating behaviors, the diary’s daily energy intake, and other nutritional reports will not be accessible to participants.

We will insert an intravenous (IV) catheter at the start of each visit to collect multiple blood samples throughout the day (Figs. 1, 2). To avoid interference with cortisol analysis during a later stress task, we will place the catheter in the morning [39]. Along with the catheter insertion, the researcher will secure the wearable wrist device onto the participant's non-dominant wrist. The device will be worn continuously for the entire day until the following morning. In the morning, we will ask participants to fill in the battery of self-reported questionnaires detailed in the “Outcomes” section below. At around 11:30, before lunch, participants will complete the first and second phase of the food choice task (FCT). At 13:30, participants will be escorted to the acclimatization room to rest before the Trier Social Stress Test (TSST). The “Procedures” section below provides detailed descriptions of both the FCT and TSST, including their structure and implementation. The stress induction phase of the TSST will begin at 14:00 and will be immediately followed by the computerized third phase—the choice phase—of the FCT. After phase three of the FCT, we will debrief the participants and serve a snack-sized portion chosen by the computer task. The visit concludes with collecting the final blood sample, at which point the IV catheter will be removed.

**Fig. 1 Fig1:**
[figure not shown]
Visits overview

**Fig. 2 Fig2:**
[figure not shown]
Baseline and post-intervention visit

#### Follow-up visit

Participants will be required to maintain a comprehensive food diary and collect one stool sample during the three days leading up to the visit. During the follow-up visit, the participant’s body weight will be measured again and they will fill in the self-reported questionnaires.

### Procedures

#### Food choice task (FCT)

We will use a FCT developed by Steinglass and colleagues to capture the participants' eating behavior [40]. The computerized task assesses maladaptive restrictive eating behavior in patients with AN, who characteristically choose low-calorie and low-fat foods. In a previous study, the task demonstrated high test–retest reliability in healthy controls [41]. Additionally, researchers validated the task in patients with AN by correlating it with their actual food consumption during a meal the following day (r = 0.61) [42, 43].

The task consists of three phases. During the first two phases, participants will view food images and rate their healthiness and taste using a five-point Likert scale, where “Healthy” to “Unhealthy” represents the health ratings, and “Good” to “Bad” represents the taste ratings. The computer will then assign a reference food item for each participant based on their input, selecting an item they rated as neutral (a score of three) for both taste and healthiness at baseline. In phase three, after undergoing the stress induction of the TSST, they will be asked to make a series of choices between their designated reference food item and other food options. The reference item is presented alongside the other food items on each trial, with the reference item displayed on the left side of the screen. Participants must indicate which item they chose to eat. They can express their preference on a Likert scale, with "strongly prefer" anchored to the left for the reference item and to the right for the other item. This phase of the task aims to capture food choices during stress. Participants are given four seconds per trial to respond during each of the three phases of the FCT. To stimulate authentic food choices, participants are informed that a snack-sized portion from one of their selected items will be served as a snack after the task. The images of the food items used in the task reflect a range of dietary choices typically found in the environment. Half of the options are high in fat, while the other half are low, defined as having less than 30% of total calories from fat. The order of the rating phases and choice trials will be counterbalanced and randomized across participants.

#### Trier social stress test (TSST)

During the baseline and post-intervention visits, participants will complete the TSST, a widely used standardized psychophysiological stress paradigm. The TSST specifically targets social-evaluative threat and perceived control, initiating a robust acute stress response that activates the sympathetic nervous system and adrenocortical stress response [44]. No significant habituation or sensitization has been found when there is a large enough interval between sequential TSSTs within a subject [45, 46]. Slight modifications are made to the speech and arithmetic part of the task to make it less predictable during the second administration.

The TSST consists of three distinct phases: an acclimatization phase, a stress induction phase, and a recovery period. The 20-min acclimatization period stabilizes the participant's physiological responses before starting stress induction. Once this period has elapsed, participants are escorted to a second room to start a five-minute task introduction. When the participant enters the second room, they encounter a two-member jury panel. The lead researcher introduces the task by reading a standardized script aloud, which informs participants that they will be required to deliver a speech for a job application in front of a panel of judges. They are told that they will have five minutes to prepare for the speech and another five minutes to deliver it and that their performance will be video recorded. Following the task introduction, participants are escorted back to the first room to begin the anticipatory stress phase, where they prepare for their mock job interview. Once this period has elapsed, the lead researcher returns participants to the second room and starts the video recording. After the researcher leaves the room, the active speech portion of the task begins, and the jury panel gives participants five minutes to deliver their speech. Upon finishing the speech, one of the panel members introduces the participant to the five-minute surprise arithmetic task for the remaining five minutes of the stress induction phase. Participants are instructed to perform a serial subtraction task where they subtract 13 from 1022 repeatedly (or 17 from 2043 during the second visit), aiming to complete as many subtractions as possible with speed and accuracy. If participants make errors, the panel members will ask them to start over from the beginning. Once the arithmetic task is complete, the lead researcher will return to the room and allow the participant to proceed to the third phase of the FCT. At the end of this task, the lead researcher and panel members will debrief the participant.

## Outcomes

### Primary and secondary outcomes

The primary outcome of this study focuses on the salivary cortisol response to acute laboratory stress. We will examine the change in cortisol levels within and between SCFAs and placebo groups. Crucial secondary outcomes encompass the participants' food choices and nutritional status (BMI). All other measures delineated in the subsequent sections serve as secondary outcome measures. See Table 1 for an overview of scheduled assessments.

**Table 1 Tab1:**
[figure not shown]
Schedule of enrolment, interventions, and assessments (SPIRIT figure)

### Measurements related to the TSST

#### Neuroendocrine measures

To measure the adrenocortical stress response during the TSST, we will collect eight saliva and four blood samples at regular intervals before, during, and after stress induction (see Fig. 3). Saliva samples will be obtained using synthetic Salivette devices and will be used to determine salivary cortisol and alpha-amylase (sAA) levels. Blood samples will be collected through an IV catheter in EDTA tubes to measure ACTH levels. After collection, all samples will be centrifuged and stored at − 80 °C until analysis by ELISA. Additionally, the participants' menstrual cycle phase and any use of hormonal contraceptives will be noted for its effect on the salivary cortisol response to acute stress.

**Fig. 3 Fig3:**
[figure not shown]
TSST and phase 3 of FCT

#### Subjective measures

To assess participants' subjective experience during the TSST, we will use Visual Analog Scales (VAS) to measure subjective stress, anxiety, perceived control, hunger, and desire to eat. We will also use the Primary Appraisal and Secondary Appraisal scale (PASA) [47], which assesses four cognitive appraisal processes of stress: threat, challenge, self-concept of own abilities, and control expectancy. Participants will complete this scale after the TSST introduction and before starting the preparation phase.

#### Physiological measures

We will monitor participants' autonomic nervous system activity during both study visits using a wrist device (Empatica EmbracePlus) that tracks heart rate response, heart rate variability, temperature, accelerometry data, and electrodermal activity. Participants will wear the device for the entire day, from the morning of the study visit until the following morning.

### Measurements related to the FCT

The FCT captures the participant's taste, health, and choice ratings on a 5-point Likert scale and their response times. The food choices made during the third phase of the FCT using the 5-point scale are converted into binary responses (yes or no preference for the 'reference item' versus the trial-unique food item). The primary outcome for the FCT is the proportion of high-fat trial-unique food items chosen over the reference item. Additionally, the proportion of self-controlled choices, choosing healthy, less tasty foods or not choosing unhealthy, tasty foods, will be evaluated as a secondary outcome.

Our objective is to measure food choices made under stress by conducting the third phase of the FCT following stress induction. After completing the FCT, participants will complete a self-developed self-report questionnaire on their subjective task experience.

### Biological samples

Blood samples for SCFA analysis will be collected via an intravenous catheter into red top serum glass tubes at five timepoints (8 am, 10 am, 12 am, 2 pm, and 4 pm) during study baseline and post-intervention study visits. The samples will be centrifuged, and the serum will be aliquoted and stored at − 80 °C for later analysis using gas chromatography-mass spectrometry. The stool samples will be used to analyze microbiota composition and quantify fecal SCFA concentrations. Stool samples are collected using in-house developed sampling devices, in which fecal matter is aliquoted during collection in wells containing 0.2 g fecal matter. These samples are sealed and immediately site-frozen at − 20 °C, and transported in a cooler within 48 h to a − 80 °C storage freezer.

